##### Clinical and explanatory data

Data for the clinical secondary outcomes and explanatory variables will be collected through existing trauma registries at the referral hospitals in Kigali and Musanze.

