### Study setting

The study will be conducted in Kigali city and Musanze district, representing areas with predominantly urban and rural catchments, respectively. In each of these areas, the public ambulance service, SAMU, carries emergency patients to all public and private health facilities. Kigali city is the capital and largest city of Rwanda, located in the nation’s geographical centre. In contrast, Musanze district is located in the Northern Province of Rwanda, making these two areas geographically separate.

In Kigali, at the time of study development, there were 5 district hospitals, 3 referral hospitals and 37 health centres (which receive less urgent cases). In 2021/2022, half of patients were transferred to three hospitals: Kibagabaga District Hospital (21%), Nyarugenge District Hospital (16%) and Centre Hospitalier Universitaire de Kigali (13%). Over 30% of patients were either transferred to health centres or managed on-site for minor cases, with the remaining patients being transferred to other hospitals (online supplemental file 1).

In the district of Musanze, Ruhengeri Level 2 Teaching Hospital (RL2TH) serves as both the referral hospital and the only district hospital. The typically patient journey for emergencies begins at the local health centre, where patients are initially triaged and stabilised. If necessary, patients are referred to RL2TH and occasionally from there to hospitals in Kigali for further treatment. There are currently no means of prioritising patients in health centres for transfer, and 912Rwanda will be used in this case to triage patients from local health centres to RL2TH, and subsequently, to the appropriate hospital in Kigali. In Musanze, there are five available ambulances, with two typically occupied with transferring patients to Kigali and a dedicated team of seven nurses who oversee prehospital care.

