### Eligibility criteria

The eligibility criteria for patient inclusion differ between the two study sites. In Kigali, all patients transferred from the incident site to a treatment facility will be included in the analysis. This encompasses transfers to both public and private health facilities within the city. In Musanze district, given that the majority of emergency patients first present to a health centre, and therefore ambulance services to pick patients up from the scene of the emergency are absent, the study will include patients transferred from health centres to the local hospital. However, patients transported from Musanze hospital to a hospital in Kigali will not be counted in the analysis.

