### Intervention

The intervention, 912Rwanda, consists of an interface on mobile devices used by ambulances and hospital staff, computer interfaces for dispatch centre staff and a software platform. 912Rwanda will be developed in multiple phases. The focus of this research is on phase two; however, the effect of phase one will also be measured.

Phase one of 912Rwanda involves the development and roll-out of software only in Kigali for ambulance dispatch to collect incident details, use global positioning system (GPS) to locate and navigate to emergencies, and enable ambulance staff to receive information. It also includes an short message service (SMS) tool for communicating incident details to receiving facilities. This phase has been fully implemented in Kigali.

Phase two of 912Rwanda will focus on the development and integration of the DDSA into the software in Kigali and Musanze, the integrated DDSA 912Rwanda platform. In Musanze, a modified version of phase two of 912Rwanda will be implemented based on local needs. The DDSA will use decision algorithms to match the patient to the closest ready facility, accounting for patient medical needs and proximity. The DDSA then alerts the ambulance teams and/or dispatch of the selected facility and the rationale for this. This decision is either approved or overridden. If approved, the ambulance proceeds to the facility. If over-ridden, the ambulance team and/or dispatch (to be decided) manually enters their choice of facility and their rationale for this by means of a pre-populated survey form.

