#### Data collection

Data to support the CCA will be collected from hospital records/databases, the trauma registry, and supplemented by insurance databases if necessary. Resources associated with the development and operating costs of 912Rwanda have been recorded and will be attributed to the eligible population of those who have and those who could have used the intervention to assign a cost per person for the intervention.

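### Kigali mortality, stay and ICU outcomes come from referral-hospital registries, whose intake the phase two algorithm can change, so phase two and combined clinical effects are liable to selection bias

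*Protocol article*

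**What the plan says.** Four parts of the protocol article bear on this.

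- **Source.** Under Clinical and explanatory data, the article states: "Data for the clinical secondary outcomes and explanatory variables will be collected through existing trauma registries at the referral hospitals in Kigali and Musanze". Objective 1 names no other source for these variables. The time outcomes have their own source, the time data collection app and the 912Rwanda platform (Time data).
- **Population.** Eligibility criteria: "In Kigali, all patients transferred from the incident site to a treatment facility will be included in the analysis", and "This encompasses transfers to both public and private health facilities within the city".
- **Where patients go.** Study setting says that in Kigali "there were 5 district hospitals, 3 referral hospitals and 37 health centres (which receive less urgent cases". Half of patients in 2021/2022 went to three hospitals: "Kibagabaga District Hospital (21%), Nyarugenge District Hospital (16%) and Centre Hospitalier Universitaire de Kigali (13" (the last figure being 13%). It adds: "Over 30% of patients were either transferred to health centres or managed on-site for minor cases". The remainder went to other hospitals.
- **What phase two does.** Intervention: "The DDSA will use decision algorithms to match the patient to the closest ready facility, accounting for patient medical needs and proximity". Staff can approve or override the choice.

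The clinical secondary outcomes are in-hospital mortality, length of stay and need for intensive care. For Kigali, the article plans separate effects for phases one and two and a combined effect (What we will estimate). Allowance for confounders looks for changes in patient characteristics over time and, if there are any, adjusts for them or interprets with caution.

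**The concern.** The stated source covers one type of hospital, while the stated population covers all destinations. That alone would only limit generalisability. The difficulty is that the phase two algorithm acts on destination. Whether a Kigali patient appears in a referral-hospital registry is then partly a result of the intervention, and a before-and-after series among registry patients conditions on something that happens after the intervention. Mortality, stay or ICU use in the registry could rise or fall because a different mix of patients arrives, with no patient's outcome changed.

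The safeguard has the same weakness. The characteristics used in the confounding check are assigned to the same registries, so as written they describe the selected patients and not all eligible trips. At stake is whether the trial can say anything causal about clinical outcomes of phase two in Kigali, and whether those results can stand as consequences in the cost-consequence analysis.

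**Working it through.** **Coverage from the document's own figures (Study setting, all patients, 2021/2022)**

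1. Check of the stated half: 21 + 16 + 13 = 50%. It reproduces.
2. Other hospitals: 100 − 50 − 30 = 20%. The health-centre and on-site share is over 30%, so this is under 20%.
3. Referral hospitals, as a share of all patients: 13% if none of the other-hospital patients went to a referral hospital, and under 13 + 20 = 33% if all did. This takes the university hospital centre as a referral hospital, which the text implies but does not state.
4. Referral hospitals, as a share of hospital-transferred patients, with the health-centre and on-site share set at 30%: 13/70 = 19% to 33/70 = 47%.
5. Hospital-transferred patients outside the registries: 37/70 = 53% to 57/70 = 81%.

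Step 4 is the fairer basis for in-hospital outcomes. Patients managed on site are not transfers, and in-hospital mortality, stay and ICU need concern hospital patients.

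**Illustration of the mechanism (all rates assumed; none is in the documents)**

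Take hospital-transferred patients in two strata with fixed mortality, so that the intervention has no true effect. Let p be the severe share, m_s and m_n the mortality in severe and non-severe patients, and r_s and r_n the proportions of each taken to a referral hospital. Then

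registry mortality = [p·r_s·m_s + (1 − p)·r_n·m_n] / [p·r_s + (1 − p)·r_n].

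With p = 15%, m_s = 10%, m_n = 1%, and r_s = 50%, r_n = 30% before phase two:

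- before: (0.0075 + 0.00255) / (0.075 + 0.255) = 0.01005/0.33 = 3.05%
- mortality in all these patients, before and after: 0.15 × 10% + 0.85 × 1% = 2.35%

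| r_s / r_n after | Registry mortality after | Ratio to before |
|---|---|---|
| 50% / 30% (unchanged) | 3.05% | 1.00 |
| 70% / 30% | 0.01305/0.36 = 3.63% | 1.19 |
| 80% / 20% | 0.0137/0.29 = 4.72% | 1.55 |
| 40% / 30% | 0.00855/0.315 = 2.71% | 0.89 |

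With p = 25% as well, and with mortality of 20% and 2% as well, the ratios are 1.17 to 1.19 (70/30), 1.46 to 1.55 (80/20) and 0.89 (40/30). Unchanged routing always gives 1.00.

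**The confounding check under the same assumptions**

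In the 80/20 row, the severe share among registry patients goes from 0.075/0.33 = 23% to 0.12/0.29 = 41%, while it stays at 15% among all hospital-transferred patients. A check on registry data would see this shift. For the clinical outcomes that is a useful warning. For the primary time outcome, which covers all trips, it would signal a change in patients that did not occur.

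**The case against.** The strongest case against runs as follows.

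- **Musanze.** One hospital is both the referral hospital and the only district hospital, and the included patients are those transferred to it. Re-routing between hospitals cannot alter registry entry there. This stands.
- **Phase one.** It brings dispatch software, GPS and SMS, with no destination algorithm. The argument does not reach the phase one effect taken alone. This stands.
- **Size and direction.** The documents give no routing or severity data after the algorithm starts, and staff may override it. The bias is zero if the referral-hospital case mix does not change. A reader might infer that the clinical estimates are biased. The documents support only that they are liable to be.
- **Denominator.** A reader might infer that two-thirds or more of the relevant patients are lost. That figure uses all patients, including those managed on site. Among hospital-transferred patients the loss is 53% to 81%. The shares also describe patients in general, while the study concerns injured people, whose split is not given.
- **Existing safeguard.** The confounding check could catch part of a case-mix shift through age, sex, complaint type and triage score. This stands in part: it works only for measured case mix, and it leads to adjustment or caution, not to a defined population.
- **Covariates.** Some probably exist outside the registries. Table 2 lists call location and condition, and quantitative implementation data come from the 912Rwanda databases. The loss for adjusting the primary outcome may therefore be smaller than the stated source implies, and that adjustment is conditional anyway.
- **Condensed article.** The sentence on sources does not say that the registries are the only source, and a full protocol may describe linkage. But the article does name a source that does not match its stated population, and its limitations section discusses data-collection differences without mentioning registry coverage.

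**Conclusion.** The point holds for Kigali, for the phase two and combined effects on in-hospital mortality, length of stay and ICU need. As written, these outcomes are observed in about 19% to 47% of hospital-transferred patients (13% to under 33% of all patients), and the intervention can change which patients those are. The estimates are liable to selection bias whose size and direction the documents do not allow one to state. The ratios of 0.89 to 1.55 only illustrate the mechanism.

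This rests on three assumptions: the university hospital centre is a referral hospital, the 2021/2022 shares for all patients roughly describe the study's patients, and no further source is used for the clinical outcomes.

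Two wider readings are not supported. The primary outcome is not undermined: its times come from the app and the platform, and only a registry-based covariate adjustment of it would be affected. Nor do the costs rest on the registry alone, since for the cost-consequence analysis the article says: "Data to support the CCA will be collected from hospital records/databases, the trauma registry, and supplemented by insurance databases if necessary".

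**What to change.** 1. In Clinical and explanatory data, Data analysis overview and What we will estimate, state that the Kigali clinical outcomes refer to referral-hospital registry patients.
2. Report, by period and as its own weekly series, the share of eligible Kigali trips taken to referral hospitals and the share captured in the registry, with case mix. Take destination from trip or platform data. The article does not say whether the baseline app or paper records hold destination, so this needs checking for the combined effect.
3. State in advance that, if that share or case mix changes, the Kigali phase two and combined results for mortality, stay and ICU are descriptive, with no intervention-effect claim.
4. For the confounding check and any adjustment, use trip-level covariates where they are held, rather than registry data alone.
5. Where the hospital records planned for the cost analysis already cover other receiving hospitals, use them to extend outcome capture. Adding only the two named district hospitals would leave three other district hospitals and the private facilities uncovered, and abstraction would have to reach back to the July 2022 baseline. This step therefore supplements items 1 to 3 and does not replace them.
6. Add the selection to Strengths and limitations.

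Items 1, 3 and 6 are wording. Items 2 and 4 need a little more analysis, and item 5 depends on what the cost analysis already collects. The price is a weaker claim for the clinical secondary outcomes.

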### Sample size calculation

For Kigali, which has two phases of the intervention, the sample size is based on the number of expected observations per week (ie, number of ambulance calls) of at least 50. The sample size includes 31 weeks of baseline data, 87 weeks of phase one implementation and 87 weeks of phase two implementation. We have assumed a realistic auto-regressive correlation of order 1 (exponential decay) to summarise the data’s correlation structure. A moderate effect size (standardised effect size of 0.5) is assumed, accounting for the total effect size, which is the sum of the expected level change and trend change in the two phases over the SD. This standardised effect size of 0.5 represents a target effect of half of the SD of the outcome across weekly time periods.

For example, if the average time from ambulance call to facility arrival has a mean of 70 min and SD of 30 (across 108 weeks), this would be equivalent to a total intervention effect of 15 min. A total sample size of 108 observations (weekly means of duration from ambulance deployment to hospital), with an equal number of observations across the three periods, would provide more than 80% power across nearly all auto-regressive correlations (autocorrelation <0.7) at 5% significance. This is a conservative estimate as we have over 87 weekly observations in each post-roll-out period for both phases of the intervention.

For Musanze, which has only one phase of the intervention, we use a similar approach but adjust for the simpler design. The sample size includes 104 weeks of baseline data and 48 weeks of phase two implementation. Assuming the sample weekly rate of ambulance calls, same auto-regressive correlation structure and a moderate effect size (standardised effect size of 0.5), which is the sum of the expected level and trend change in the one phase intervention over the SD, a total sample size of 72 observations would provide more than 80% power across all auto-regressive correlations values of less than 0.6.

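### The stated power above 80% (108 weekly means in Kigali, 72 in Musanze) does not fit the plan's own effect size of half a weekly SD for level and trend change together

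*Protocol article*

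**What the plan says.** All inputs are in the Protocol article, Sample size calculation (Objective 1).

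- **Effect:** 0.5, described as "the total effect size, which is the sum of the expected level change and trend change in the two phases over the SD". The section adds that this "represents a target effect of half of the SD of the outcome across weekly time periods".
- **Example:** "a mean of 70 min and SD of 30 (across 108 weeks"), giving a total effect of 15 min.
- **Kigali:** 108 weekly means in three equal periods "would provide more than 80% power across nearly all auto-regressive correlations (autocorrelation <0.7) at 5% significance".
- **Musanze:** "a total sample size of 72 observations would provide more than 80% power across all auto-regressive correlations values of less than 0.6".
- **Margin, Kigali:** "This is a conservative estimate as we have over 87 weekly observations in each post-roll-out period". The same section gives 31 weeks of baseline.

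The Data analysis section plans a segmented model with time, phase indicators (roll-out included) and time-by-phase interactions. It will report shift changes and trends with 95% CIs and, in Kigali, a linear combination over both phases. The Intervention section says: "The focus of this research is on phase two; however, the effect of phase one will also be measured".

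**The concern.** Half an SD of the weekly series is a small signal for 36 weeks per period, even with no trend terms and no autocorrelation. The planned model adds a trend in every segment, and positive autocorrelation reduces the information further. Yet the plan states more than 80% power up to correlations of 0.6 or 0.7.

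The definition is also incomplete. A level change is in minutes and a trend change in minutes per week, so their sum has no meaning until a week is named at which it is taken.

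At stake is how the results are read. Someone relying on the stated power would take a wide or null estimate as coming from a study able to detect 15 min. The section also gives no power for phase two alone in Kigali, because the 0.5 is shared across both phases although phase two is the focus.

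**Working it through.** **Inputs.** Effect d = 0.5 in units of the marginal SD of the weekly series; 36 weeks per period; AR(1) errors with correlation ρ; 5% significance. Assumptions: two-sided test (sidedness is not stated), 36/36 split of the 72 Musanze weeks (not stated; an even split is the most favourable), ρ ≥ 0 and known. Power = Φ(d/SE − 1.96) + Φ(−d/SE − 1.96). For ρ > 0 the SE is the exact generalised least squares value.

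**Step comparison, no trend terms, ρ = 0**
- 36 v 36: SE = √(1/36 + 1/36) = 0.236; d/SE = 2.12; power 56%.
- Kigali, 36 v 72 (both post-periods pooled, whole effect present from phase one): SE = √(1/36 + 1/72) = 0.204; d/SE = 2.45; power 69% (79% one-sided).

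**Segmented model, ρ = 0.** With 36 weekly points, Sxx = 36(36² − 1)/12 = 3885. A fitted line at distance x from the segment's mean time has variance 1/36 + x²/3885.
- Level change: post-period line at its first week (x = 17.5) gives 0.107; baseline line projected to that week (x = 18.5) gives 0.116. SE = √0.2225 = 0.472; power 19%.
- Level plus trend at the last week of a 36 + 36 series: baseline projected to x = 53.5 gives 0.765. SE = √(0.765 + 0.107) = 0.933; power 8%.
- Same total at the last of 108 weeks: x = 89.5 gives 2.090. SE = √(2.090 + 0.107) = 1.48; power 6%.

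**Power by autocorrelation**

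| Contrast, d = 0.5 | ρ = 0 | 0.3 | 0.6 | 0.69 |
|---|---|---|---|---|
| Step, 36 v 36 | 56% | 36% | 22% | 20% |
| Step, 36 v 72 pooled (Kigali) | 69% | 45% | 27% | 23% |
| Segmented level change | 19% | 13% | 11% | 11% |
| Segmented total, end of 36 + 36 | 8% | 7% | 6% | 6% |
| Segmented total, end of 108 weeks | 6% | 6% | 5% | 5% |

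Simulation with ρ estimated (Prais-Winsten, 3000 runs per cell) agrees closely at ρ = 0: 57% for the step and 21–22% for the segmented level change. At ρ = 0.6 it gives 17–18% for the level change, but with type I error of about 11% in the 36 + 36 series.

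For 80% power at ρ = 0 the step needs 2.80 × 0.236 = 0.66 SD (about 20 min at SD 30). The segmented level change needs 2.80 × 0.472 = 1.32 SD (about 40 min).

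**Readings that do exceed 80%**
- *Trend change entered as a slope per week.* Splitting 0.5 over four Kigali coefficients gives 0.125 SD/week. A test of that slope has 85% power at ρ = 0.6 and 77% at 0.69; the same slope in 36 + 36 weeks has 84% at 0.6. This resembles the stated cut-offs, but 0.125 × 30 = 3.75 min/week, and 3.75 × 36 = 135 min, not a total of 15 min.
- *SD of 30 taken between calls.* With at least 50 independent calls a week, the SD of the weekly mean is 30/√50 = 4.24 min, so 15 min is 15/4.24 = 3.5 weekly SD. The level change then has more than 99% power. The text, however, scales the effect by the SD across weeks.

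**Real Kigali calendar, ρ = 0.** The Intervention timeline gives roll-out periods of about 39 weeks (March–November 2023) and 13 weeks (August–October 2025). These are taken as fitted separately, so they do not inform the baseline line.
- Phase-one level: baseline of 31 weeks, Sxx = 31 × 960/12 = 2480, projected x = 55 weeks: 1/31 + 55²/2480 = 1.252. Phase-one line (87 weeks, Sxx = 54,868) at its first week: 1/87 + 43²/54,868 = 0.045. SE = √1.297 = 1.14 SD; power 7%.
- Phase-two level: phase-one line projected x = 57: 1/87 + 57²/54,868 = 0.071; plus 0.045. SE = √0.116 = 0.34 SD; power 31% if phase two carries the whole 0.5, 11% if it carries half.

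**Real Musanze calendar** (104 and 48 weeks, roll-out gap about 22): level change 25% at ρ = 0 and about 11% at 0.6.

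**The case against.** The strongest defence is that the calculation was sound and only its description is loose. The per-week slope reading comes close to the stated cut-offs at both sites, and an article may condense a fuller simulation. The SD of 30 is also hard to believe as an SD of weekly means: with 50 independent calls and no other week-to-week variation, it would imply a between-call SD of 30 × √50 = 212 min on a 70-min mean. This stands in part. The fault may lie in the stated effect or SD rather than in the computation, and a miscalculation is not shown. The text as printed is still inconsistent, because both rescuing readings contradict it.

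A reader might infer that the study is underpowered to detect 15 min. The documents do not support that. If the weekly SD is nearer 4.2 min, the phase-two level changes would be well powered and even the Kigali phase-one level change would have about 87% at ρ = 0 (3.54/1.14 = 3.10).

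A reader might also reject the conservative label outright. That goes too far. The sentence concerns the post-roll-out periods, and phase two does gain from them: its level change rises from 19% to 31%, and a no-trend comparison of phase two with phase one (87 v 87) has 91% at ρ = 0, though 39% at 0.6. Likewise, a no-trend step in Musanze on the real calendar has 82% at ρ = 0. Those are not the planned model, and they drop well below 80% at the correlations claimed.

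Finally, the plan names no end-of-period contrast. The 5–8% figures show what one natural choice of week implies, not what the plan commits to. Keeping the combined effect as a main estimate is a design choice and not an error.

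**Conclusion.** The concern holds as an inconsistency between the effect-size definition and the stated power. On that definition, with 36 weeks per period and ρ ≥ 0, none of the contrasts examined reaches 80%. The best is 69% two-sided (79% one-sided), and it needs ρ = 0, no trend terms and the full effect from the start of phase one. At the upper correlations claimed, the most favourable step tests give 22–23%, and the planned segmented level change has about 11%.

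The conservative label does not hold for the Kigali phase-one and combined effects, which rest on 31 baseline weeks (fewer than the 36 assumed) and a 39-week projection. It holds in direction for phase two, though the level-change power stays far below 80%.

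The result assumes a two-sided test, non-negative AR(1) correlation (at about −0.3 a simple step test would pass 80%), and an even split in Musanze. Power in minutes remains open until the SD scale is settled.

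**What to change.** In the sample size section, state for each site:

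- the level change in minutes and the slope change in minutes per week;
- whether the SD is that of weekly means or between calls;
- the contrast tested, and the week at which level and trend are summed.

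Then recompute power, or the detectable effect in minutes, by simulation for the planned segmented model. Use the actual weeks and roll-out gaps and the weekly SD and autocorrelation seen in the series already collected. Include the phase-two effect in Kigali on its own. Replace both statements of power above 80% with the result, and limit the conservative label to contrasts for which it is true.

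The cost is one re-run and some rewording, with possibly a less favourable stated power. Neither the calendar nor the number of patients changes.
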